### Analysis Plan

#### The Child Level

##### Primary aim

The main analyses of child-level effects will employ an intention-to-treat principle, thus including all subjects and preschools originally allocated to the respective groups, to test the study’s effectiveness (Polit and Gillespie, 2010). However, as shown for the school setting (Donnelly et al., 2009), there are strong arguments for including per-protocol analyses for the examination of efficacy. Therefore, we will perform secondary analyses limited to preschools that exhibit acceptable intervention adherence. Missing data will be sought, minimized, detailed, and handled in line with suggested guidelines (Little et al., 2012). Attrition analyses will be performed to investigate whether missing data are related to child characteristics. Missing data will be handled by the use of linear mixed models (LMMs) and structural equation modeling (SEM) (Enders, 2011; Little, 2013).

Intervention effects will be evaluated by testing for time^∗^group interactions for all outcomes. The per-protocol analysis will be adjusted for differences between the groups, as appropriate. LMM and multilevel SEM for mediation analyses (SEM) (Little, 2013) will be used to account for clustering of observations on the preschool level in all analyses. A two-sided *p* ≤ 0.05 is considered statistically significant; however, both ESs and patterns of effects across variables will be considered of greater importance than *p*-values when drawing study conclusions. Consistent with this approach, *p*-values will not be adjusted for multiple testing. Main analyses will be performed using IBM SPSS v. 25 (IBM SPSS Statistics for Windows, Armonk, NY: IBM Corp., United States) or later versions and MPLUS v. 8 or later versions (Muthén and Muthén, Los Angeles, United States). Reporting will be done in accordance with the CONSORT statement (Campbell et al., 2012).

We regard children’s cognition as the main study outcome. However, we include several aspects of cognition in the present study (socioemotional health, self-regulation, executive functions, and learning), of which designating one focused outcome *a priori* is challenging and inappropriate based on the current level of evidence of effects of PA in young children (Carson et al., 2016; Alvarez-Bueno et al., 2017a, b; Singh et al., 2019). These constructs will be analyzed as separate variables, to retain their unique information, as well as latent variables, to remove measurement error and establish broader constructs, and thus obtain both specific as well as broader knowledge about the effect of PA on cognitive outcomes. Children’s PA, physical fitness, motor competence, adiposity, and staff PA are regarded secondary outcomes.

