Sample-size calculations are derived from standardized ESs in meta-analyses of interventions investigating preschoolers’ objectively measured PAs (Finch et al., 2016) and motor competences (Wick et al., 2017), and schoolchildren’s cognition (Alvarez-Bueno et al., 2017b) and learning (Alvarez-Bueno et al., 2017a). Preschool interventions have shown small ESs for long-term interventions delivered by preschool staff targeting PA [ES = 0.07 (three studies, > 6 months) and 0.27 (10 studies, delivered by teachers)] (Finch et al., 2016) and motor competence [ES = 0.32 (six studies, vs 6 months) and 0.41 (eight studies, delivered by teachers)] (Wick et al., 2017). Rather similar ESs are shown for cognition (0.11-0.30) (Alvarez-Bueno et al., 2017b) and learning outcomes (0.16-0.26) (Alvarez-Bueno et al., 2017a) in older children (4-18 years). Derived from a conservative sample-size calculation using standard formulas, including correction for the cluster RCT design, we aim to recruit a minimum of 60 preschools and 800 3- to 4-year-old children to the study. This sample size will allow for uncovering statistically significant standardized ESs (Cohen’s d) of 0.25-0.30 at the 18-month follow-up, given *ɑ* = 0.05, 1-β = 80%, group ratio 1:1, correlation of repeated measurements = 0.6-0.7, intra-class correlation (ICC) across clusters = 0.05-0.10, children per cluster = 13 accounting for 30% attrition among children (median number of 3- to 4-years-old in preschools in Sogn og Fjordane ≈ 18), and coefficient of variation for cluster sample size = 0.65 (Eldridge et al., 2006). Thus, we will require ≈ 400 children and 30 preschools for analysis in each group (intervention; control), given a design effect correction factor = 1.85-2.69. The ICC is estimated using a mean ICC = 0.05 for trials investigating objectively measured PA levels in preschoolers (Finch et al., 2016), results from the Sogn og Fjordane Preschool Physical Activity Study: ICC ≤ 0.10 for PA (Nilsen et al., 2019b) and ICC ≤ 0.05 for motor competence (unpublished), and ICC = 0.07-0.09 for academic performance in schoolchildren (Resaland et al., 2016). Because the sample-size calculation is performed for the 18-month follow-up of 3- to 4-years-old, we will have increased power at the 7-month follow-up, as we also include 5-years-old (minimum total *n* ≈ 1,200 children); ESs as low as 0.20 can be detected at the 7-month follow-up under the assumptions specified above.

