#### The Preschool Level

The individual interviews and focus groups will be recorded, transcribed verbatim, and imported with field notes of observations and documents from each preschool into NVivo-11 for data management. The data will be thematically analyzed following the procedures proposed by Braun and Clarke (2006). The Normalization Process Theory will provide a conceptual framework to understand and evaluate how staff make sense of the intervention (coherence), engage with the professional development (cognitive participation), integrate PA practices in their preschool’s daily practices (collective action), and evaluate the effects of improved quality and quantity of PA practices into their daily operations (reflexive monitoring). Data will be analyzed subsequently and arranged into, within, and between preschool data displays to explore convergences and divergences between the case study preschools. The preliminary displays will also help to identify potential themes and gaps in the data that need to be explored during the second and third round of data collection.

Staff PA will be analyzed using similar statistical approaches as described for child-level outcomes above (i.e., effects will be determined using a between-group comparison). For other data, analyses will be restricted to examination of main effects of time because we only include repeated measurements for the intervention group. Preschool level data will be used as a basis for per-protocol efficacy analyses of individual level outcomes. For these analyses, preschool level data will be used to decide which preschools should be included using appropriate cut points for acceptable participation and engagement in the intervention activities and/or by including these data as explanatory variables in regression models. In association analyses between individual and preschool level data, data will be combined using preschool averages.

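### The secondary per-protocol analysis selects preschools on adherence that only the intervention arm can show, so it should not be presented as an examination of efficacy

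*Protocol article*

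**What the plan says.** Under Analysis Plan, The Child Level, Primary aim, the article makes intention-to-treat the main analysis, with all preschools and children kept as allocated. It then argues that a per-protocol analysis is needed to examine efficacy and states "we will perform secondary analyses limited to preschools that exhibit acceptable intervention adherence". That analysis is to be adjusted for group differences where suitable; no covariates are named.

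Under Analysis Plan, The Preschool Level, it adds that "preschool level data will be used to decide which preschools should be included using appropriate cut points for acceptable participation and engagement". As an alternative or addition, the same data may enter regression models as explanatory variables. Apart from staff physical activity, repeated preschool-level measurements exist only for the intervention group.

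Two measurement sections matter here. Attendance and task completion in the professional development are logged (Participation and engagement in professional development). The MOVERS rating of the movement environment is taken in all rooms at baseline, and later only in the intervention group (Observation of the movement environment).

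**The concern.** An efficacy comparison should contrast like with like. Here a preschool stays in the analysis because of something it did after allocation, and only one arm had the opportunity to do it. Control preschools receive no course, so no participation criterion can apply to them. The natural inference, which the article does not state, is that adherent intervention preschools will be compared with all controls.

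The selection factor is plausibly prognostic on the article's own reasoning. The Introduction ties successful promotion of activity to competent, motivated directors and staff, and the account of the preschool-level intervention gives the director a pivotal role. Preschools with such staff may see better child development without the programme.

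At stake is a secondary claim that the programme works where it is properly implemented. The article gives effect sizes and patterns more weight than p-values and makes no multiplicity adjustment, so a modest spurious effect could carry weight in the interpretation.

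**Working it through.** **1. The plan's own figures.** No stated figure depends on the per-protocol set, but the sample-size section supplies the scale. Inputs from Participants: "of 0.25-0.30 at the 18-month follow-up", "group ratio 1:1", 80% power, "correlation of repeated measurements = 0.6-0.7, intra-class correlation (ICC) across clusters = 0.05-0.10", "children per cluster = 13 accounting for 30% attrition among children" and "coefficient of variation for cluster sample size = 0.65". The two-sided 5% level is in Primary aim.

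- Children per preschool before rounding: 18 × 0.70 = 12.6.
- Design effect = 1 + ((CV² + 1)m − 1) × ICC. With CV² = 0.4225 this is 1 + 16.92 × 0.05 = 1.85 and 1 + 16.92 × 0.10 = 2.69, as stated.
- Detectable d = (1.96 + 0.84) × √(2 × 2(1 − r) × design effect / n). With r = 0.6 and n = 30 × 12.6 = 378 per arm this is 0.248 at ICC 0.05 and 0.299 at ICC 0.10, matching 0.25-0.30.

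The sample-size figures therefore reproduce. ICC 0.05 pairs with 0.25 and ICC 0.10 with 0.30.

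**2. Spurious effect with no true effect.** Assumptions that are not in the article: share of preschools kept (π) 50-90%; correlation (ρ) 0.3-0.5 between a preschool's adherence and its baseline-adjusted outcome tendency; r = 0.65, the middle of the stated range, at preschool as well as child level; all controls retained.

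- SD of the baseline-adjusted preschool component = √(ICC × (1 − r²)) = √(0.05 × 0.5775) = 0.170 or √(0.10 × 0.5775) = 0.240.
- Mean of the top share π of a standard normal = φ(z)/π, where z is the cut-off: 0.798 at 50%, 0.497 at 70%, 0.195 at 90%.
- Bias = φ(z)/π × ρ × SD. Smallest: 0.195 × 0.3 × 0.170 = 0.010. Largest: 0.798 × 0.5 × 0.240 = 0.096.

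Simulation of 20,000 trials per setting (30 v 30 preschools, 13 children each, t-test on preschool means) agrees:

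| Kept | ρ | Bias, ICC 0.05 | Bias, ICC 0.10 | Rejection, ICC 0.05 | Rejection, ICC 0.10 |
|---|---|---|---|---|---|
| 50% | 0.3 | 0.040 | 0.058 | 7.5% | 8.7% |
| 50% | 0.5 | 0.067 | 0.096 | 11.5% | 15.5% |
| 70% | 0.3 | 0.026 | 0.035 | 6.4% | 6.7% |
| 70% | 0.5 | 0.043 | 0.059 | 8.3% | 9.9% |
| 90% | 0.3 | 0.010 | 0.014 | 4.9% | 5.4% |
| 90% | 0.5 | 0.017 | 0.024 | 5.9% | 6.0% |

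At ρ = 0 the bias is zero and rejection is about 5%.

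A pure change contrast has SD √(2(1 − r) × ICC). At r = 0.65 this is √(0.70/0.5775) = 1.10 times as large, so the order of magnitude is the same. It is smaller if preschool levels are more stable over time than r = 0.65.

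**3. With a true effect.** If adherent preschools alone gain 0.25 SD, the subset contrast gives 0.26-0.35 over the same settings, while intention-to-treat divided by the adherent share gives 0.25.

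**4. Limit of that rescaled estimate.** If 70% adhere and gain 0.25 but the other 30% gain half of it, intention-to-treat = 0.7 × 0.25 + 0.3 × 0.125 = 0.2125. Dividing by 0.7 gives 0.30, an overstatement.

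**The case against.** The strongest reply is that the analysis is secondary, is adjusted, and leaves the main result alone. Several parts of this stand.

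- Intention-to-treat is the declared main analysis. A reader might infer that the trial's principal conclusion is exposed; it is not.
- Effects are tested as time-by-group interactions, so stable preschool differences cancel. A reader might compute the bias from follow-up levels. Keeping 20 of 30 preschools, 0.545 × √0.10 = 0.17 at a correlation of 1, which against 0.20 is 85% of a target effect. That reading fails: it ignores the baseline measurement, needs a perfect correlation, and sets the ICC 0.10 bias against the 7-month figure of 0.20.
- Baseline MOVERS scores cover both arms, so part of preschool quality can be adjusted for. This reduces confounding but does not remove what is unmeasured.
- The article also allows adherence as a regression covariate, so subsetting is not the whole plan. That route still conditions on engagement after randomization.
- A condensed article may leave numerical cut points to a fuller document, so their absence is not a fault. Nor does the article say they will be chosen after results are seen. Data Management locks the database before allocation is opened and before any analysis, though it does not say that the adherence rule is fixed by then.
- A complier-average effect is no assumption-free substitute. Equipment, the web toolbox and continuing support are provided to the intervention preschools alongside the course, and the research group works with the entire staff (Intervention and Theoretical Framework, and its section The Preschool Level). Allocation may therefore act by routes other than logged participation.

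None of this makes the adherent subset a randomized comparison.

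**Conclusion.** The point holds for the secondary analysis and its label. Selection on adherence can act only in the intervention arm, and the planned adjustment cannot restore the balance that randomization gave. The spurious effect is about 0.01-0.10 SD, with 5-16% rejection at a nominal 5%, if 50-90% of preschools adhere and adherence correlates 0.3-0.5 with the baseline-adjusted outcome tendency. Set against the matching 18-month targets, the largest values are 0.067/0.25 = 27% and 0.096/0.30 = 32%. The adherence share, the correlation and its positive sign are assumptions, and retaining all controls is an inference. With zero correlation there is no bias. The documents do not support the further inference that the subset result must exceed intention-to-treat.

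**What to change.** - Label the adherent-subset result, and any model with adherence as a covariate, non-randomized and exploratory. Do not present either as efficacy.
- Fix the adherence measure and rule from the participation log before allocation is opened to the analysts. Adjust for baseline outcome and baseline MOVERS.
- Add, rather than substitute, an instrumental-variable (complier-average) estimate: randomized arm as instrument, logged dose as exposure with controls at zero, and standard errors clustered by preschool. State that it assumes no effect of allocation except through participation, and why equipment, toolbox and support make this doubtful here.

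The cost is one extra analysis on data already to be collected. Its interval will be wider than that of intention-to-treat, it adds no power, and it may overstate the effect if low-adherence preschools also benefit.

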##### Secondary aim

###### Secondary analyses of intervention effects

*A priori*-defined moderation and mediation analyses will be performed to study child characteristics and pathways that may be important for the effect of the intervention. For example, evidence shows that PA interventions in school are most beneficial for those most in need (Resaland et al., 2016, 2018a) and possibly more beneficial for boys than for girls (Resaland et al., 2018b). Thus, we will test for effect moderation by sex, age, socioeconomic status, and baseline levels of outcomes. We will test for mediation of effects through hypothesized pathways including self-regulation/executive functions as mediators between PA and learning (Howie and Pate, 2012), and socioemotional characteristics, physical fitness, motor skills, and adiposity as mediators between PA and cognitive outcomes (Tomporowski et al., 2011). Mediation analyses include the use of SEM. Importantly, because we include three time points, the design allows for testing a full mediation model (Little, 2013).

###### Association analyses

The large sample allows for analyses of distributions and correlates among the included variables in cross-sectional analyses, as well as analyses of development and tracking over time, and analyses of determinants of change in outcomes in longitudinal analyses in the control group. Cross-lagged panel analysis will be used to determine reciprocal relationships among variables over time (Little, 2013). If there are small and non-significant intervention effects, longitudinal analyses will include both groups to increase power of these analyses. In addition to standard regression models, we will use multivariate pattern analysis (Aadland et al., 2018a, b) to explore multivariate association patterns among the included variables. These analyses include associations related to intervention effects performed by associating changes over time (exposure) to group (outcome), to support the interpretation of the study effects. Multivariate pattern analysis will be performed in Sirius v.11 (Pattern Recognition Systems AS, Bergen, Norway); otherwise, we will use the same statistical models (LMM and SEM) and software, as specified above.

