##### The “Motor challenging physical activity” component

Learning to move is essential for PA, and during the early years, children acquire competence in diverse fundamental movement skills, such as locomotion and object control (Stodden et al., 2008). Motor competence has been suggested to be a primary underlying mechanism that promotes engagement in PA, both acutely and over the long-term. A conceptual model by Stodden et al. (2008) proposes a synergistic relationship among motor competence, perceived motor competence, PA, physical fitness, and weight status. During the early years, the child’s perception of their motor competence is especially important, as children with high perceived motor competence are more persistent and engaged in various activities. Importantly, their perceived motor competence might be weakly correlated to their actual motor competence (Stodden et al., 2008). As such, an intervention aiming to improve motor competence might benefit from building children’s perceptions of their motor competence. Moreover, both AGT and SDT emphasize perceived competence as an important psychological factor (Robinson et al., 2015), which may act as a mediator between actual motor competence and actual/future PA, as well as various developmental outcomes. Robinson et al. (2015) reviewed the proposed links in the conceptual model by Stodden et al. (2008) and concluded that motor competence and PA are weakly to moderately associated in early and middle childhood. This is consistent with results from a large Norwegian study in preschoolers, which extends these results by showing that the association pattern between PA and motor competence is characterized particularly by vigorous intensities (Nilsen et al., 2019a).

Importantly, motor competence will likely not be optimally stimulated through naturally occurring behaviors and thus needs to be taught (Stodden et al., 2008; Robinson et al., 2016). Furthermore, to optimally promote motor competence, it is important to provide challenging activities that keep the children on a positive trajectory of learning and maximize motivation and engagement (Robinson et al., 2015). Consistent with the Challenge Point Framework (Guadagnoli and Lee, 2004), the ACTNOW intervention seeks to adapt intervention activities that are developmentally appropriate and individually adapted in order to meet each child’s optimal challenge point.

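### An ordinary cross-lagged panel model can show paths in both directions that come only from stable differences between children, so reciprocity should not be concluded from it alone

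*Protocol article*

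**What the plan says.** The Association analyses subsection (secondary aim, child level) states: "Cross-lagged panel analysis will be used to determine reciprocal relationships among variables over time". The data are first the control arm, through "analyses of determinants of change in outcomes in longitudinal analyses in the control group". If intervention effects are small and non-significant, "longitudinal analyses will include both groups to increase power of these analyses". The model family is fixed only broadly: "otherwise, we will use the same statistical models (LMM and SEM) and software, as specified above". No within-child or random-intercept form is named, and none is excluded.

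Two other features bear on the point. Primary aim plans to analyse the cognition constructs as separate variables "as well as latent variables, to remove measurement error and establish broader constructs", and it accounts for clustering at preschool level. The section on secondary analyses of intervention effects notes that "because we include three time points, the design allows for testing a full mediation model". Three waves are also the minimum for a cross-lagged model with random intercepts.

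**The concern.** A cross-lagged path is the coefficient of X at one wave when Y at the next wave is regressed on X and Y at the earlier wave. One earlier Y score is an imperfect marker of a child's stable level of Y. If stable X and stable Y are correlated across children (through family background, maturity or temperament, say), the earlier X score picks up part of the stable Y level that the earlier Y score missed. The path is then non-zero without any effect of X on Y. The same holds in the other direction, so the result looks like a reciprocal relationship.

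Neither feature above fully removes this. Latent variables deal with measurement error in their indicators, not with stable differences between children. The preschool level sits above the child. At stake is how links among activity, motor skills, fitness, self-regulation and cognition are reported. The pooling rule adds to the exposure: the larger sample is used when the randomised effects are small and non-significant.

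**Working it through.** **Inputs**

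- Repeat correlation r: "correlation of repeated measurements = 0.6-0.7" (Participants); midpoint 0.65 used.
- Children: about 400 per arm (Participants), so about 800 if both arms are pooled.
- Test level: two-sided 0.05 (Primary aim).
- Cross-sectional correlation ρ between two variables: not given. The article says only that "motor competence and PA are weakly to moderately associated in early and middle childhood". Assumed range 0.1 to 0.3.
- Split of ρ between stable levels and occasion fluctuations: not given. Three cases are shown.
- Preschool clustering is left out.

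**The plan's own figures.** None is stated for the cross-lagged analysis. The sample-size figures that supply r and n do reproduce. With 18 × 0.7 = 12.6 children per cluster, the design effect is 1 + ((0.65² + 1) × 12.6 − 1) × ICC = 1.846 at ICC 0.05 and 2.692 at 0.10 (stated 1.85-2.69). With 30 × 12.6 = 378 per arm and r = 0.6, the detectable d is 2.80 × √(2 × DE/378 × 2(1 − 0.6)) = 0.248 and 0.299 (stated 0.25-0.30).

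**Spurious path.** With standardised variables and no cross-effects,

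path = (c − ρr)/(1 − ρ²),

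where c is the correlation of X at one wave with Y at the next. Take each score as a stable part (variance share r) plus independent occasion noise, with the noise of X and Y correlated ρe within a wave. Then c = ρ − (1 − r)ρe.

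At ρ = 0.2, r = 0.65:

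- All correlation in the stable levels (ρe = 0): c = 0.2, path = (0.2 − 0.13)/0.96 = 0.073.
- Occasion parts correlated half as strongly as the total (ρe = 0.1): c = 0.2 − 0.35 × 0.1 = 0.165, path = 0.035/0.96 = 0.036.
- Occasion parts correlated equally (ρe = 0.2): c = 0.2 − 0.35 × 0.2 = 0.13 = ρr, path = 0.

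**Rejection rate.** SE = √[(1 − R²)/((n − 3)(1 − ρ²))]. In the first case the coefficient of Y's own earlier score is (0.65 − 0.2 × 0.2)/0.96 = 0.635, so R² = 0.635 × 0.65 + 0.073 × 0.2 = 0.428. At n = 400, SE = √(0.572/(397 × 0.96)) = 0.039 and z = 1.88, giving a rejection rate of 47%. At ρ = 0.3 the path is 0.105/0.91 = 0.115, SE 0.040, z = 2.92, rate 83%.

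| Per-path false rejection, n = 400, r = 0.65 | ρ = 0.1 | ρ = 0.2 | ρ = 0.3 |
|---|---|---|---|
| All correlation in stable levels | 15% | 47% | 83% |
| Occasion parts correlated half as strongly as the total | 7% | 16% | 30% |
| Occasion parts correlated equally | 5% | 5% | 5% |

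Simulations with other mixes of stable and autoregressive variance, at the same repeat correlation, gave nearly the same rates: 14-15%, 46-47% and 83-84% in the first row. With no stable part at all (pure autoregression), rejection stayed at 4-5%.

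**Sensitivity in the first row at ρ = 0.2.** At r = 0.6 the path is 0.2 × 0.4/0.96 = 0.083 (SE 0.041, rate 53%). At r = 0.7 it is 0.2 × 0.3/0.96 = 0.063 (SE 0.036, rate 40%). With 280 children (400 less 30%) the rate is 34-38%. With both arms pooled (n = 800) it is 76-77%, and about 98% at ρ = 0.3.

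**Both directions.** In the all-stable case at n = 400, both directions were significant in at least one interval in about 35-40% of samples at ρ = 0.2 and 87-91% at ρ = 0.3.

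**Random-intercept form.** With stable share 0.5, autoregression 0.3 and stable-level correlation 0.5 (ρ = 0.25, r = 0.65), the population cross-lag is 0.093 in the ordinary model and 0.00 with random intercepts. The joint test of four cross-lags in the random-intercept model rejected in 36/910 (4.0%) at ρ = 0.2 and 39/883 (4.4%) at ρ = 0.3. A small run of a two-path test gave 7/60 (12%, 95% CI 4.8-22.6%), too few to conflict with this. The cost is precision: a cross-lag SE of about 0.08-0.11 instead of about 0.04, and joint power of 16-20% for true cross-lags of 0.10.

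**The case against.** The strongest reply is that the article names a method in one sentence and leaves its exact form open. Three waves and SEM software allow random intercepts, and a full analysis plan may specify them. This stands as a limit on what can be said: the article does not exclude the better model. But it does state what the analysis will determine, and the ordinary form cannot support that.

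A reader might infer that the authors will declare variables to drive each other. The documents do not support that. The text speaks of relationships, under a heading on associations, and the Discussion disclaims support for a specific hypothesis on activity and cognition. Nor is false reciprocity certain: it needs stable levels that correlate more strongly than the fluctuations do, and the article does not say whether they do.

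A reader might also take the model's null to be the absence of stable differences between children. It is not. The null is a zero path given earlier levels; the absence of a stable component is an assumption.

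Latent variables help in part. If the occasion noise is only indicator error, they remove it and the spurious path with it. They are planned for the cognition constructs, and real fluctuation between occasions remains.

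Primary aim ranks effect sizes and patterns above p-values, and the spurious paths are small (0.073 and 0.115 at ρ = 0.2 and 0.3). However, a consistent two-way pattern is what the artefact produces.

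Finally, random intercepts target within-child change rather than prediction between children, at low power. That argues against replacing the ordinary model outright, but not against reporting both.

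**Conclusion.** The concern holds in a limited form. The ordinary cross-lagged model can produce significant paths in both directions when neither variable affects the other, and the stated aim of determining reciprocal relationships is stronger than that model supports. The inflation ranges from none (5%) to severe (83% per path at ρ = 0.3). Where a given pair of variables falls depends on two quantities that the article does not give: their cross-sectional correlation, and how it divides between stable levels and fluctuations. The figures also assume a repeat correlation of 0.65, 400 children and no preschool clustering.

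The analysis is secondary and non-randomised. The time-by-group comparison, the sample size and the test level are untouched. This is a cheap improvement, not a flaw in the main inference.

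**What to change.** In Association analyses, state that:

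- the cross-lagged model will also be fitted with a random intercept (stable child factor) for each variable over the three time points, and reported alongside the ordinary model;
- paths from the ordinary model will be described as prospective associations (rank-order prediction);
- a reciprocal or directional relationship will not be concluded from the ordinary model alone.

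This uses the waves and SEM software already planned, so the cost is extra analysis and more cautious wording. The wider standard errors and low power shown above remain, the two-variable model has one degree of freedom for fit, and identification rests on the children followed to 18 months. A null random-intercept result should therefore be read as inconclusive, not as evidence against a reciprocal relationship.

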**FIGURE 3 F3:**
[figure not shown]
Flow chart of the study.

We will cluster randomize at the preschool level, since we regard delivery of the intervention on the preschool level the only practical approach. A third party ([name], Norwegian School of Sport Sciences) will randomize ≈ 60 preschools to the intervention group (≈ 30 preschools) or the standard of care control group (≈ 30 preschools). Randomization will be done separately in the two study waves after completing recruitment and before initiating baseline data collection using a random number generator (Stata/SE 15.1, StataCorp LLC, College Station, TX, United States). We will use block randomization (randomly chosen block sizes of 4 and 6) and a 1:1 ratio for the two intervention arms. Blinding of participants and preschools is not possible due to the nature of the experiment. To limit potential biases, the fewest possible assessors involved in project management, data collection, and statistical analysis will have knowledge about the group assignment and the study hypotheses.

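### The multivariate pattern analysis of change against group sits outside the models that handle preschool clustering, and no cluster-aware step is stated for it

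*Protocol article*

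**What the plan says.** The Protocol and Randomization section sets the unit of allocation: "We will cluster randomize at the preschool level". The two waves are randomized separately.

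Under Analysis Plan, Primary aim, the article names LMM and multilevel SEM and says that these "will be used to account for clustering of observations on the preschool level in all analyses". No other means of handling clustering is named. The same section sets the significance level: "A two-sided *p* ≤ 0.05 is considered statistically significant".

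Under Secondary aim, Association analyses, a further method is introduced to explore multivariate association patterns. One of its uses covers "associations related to intervention effects performed by associating changes over time (exposure) to group (outcome), to support the interpretation of the study effects". On software the article says "Multivariate pattern analysis will be performed in Sirius v.11", and adds that LMM and SEM serve for everything else. It does not say how a pattern would be judged present, or whether children or preschools are the unit of resampling.

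**The concern.** Children in one preschool share the group label and, to some degree, the way they change. A model that predicts group from change and counts each child as an independent observation can pick up differences between preschools and present them as differences between arms. Cross-validation does not cure this if classmates fall in both the training and the test part.

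The commitment to handle clustering everywhere rests on two model families, and this analysis is expressly placed outside both. The stated remedy therefore cannot be applied to the stated method. What is at stake is the reading of the trial's effects, because the analysis is there to support that reading. A pattern that reflects only which preschools fell in which arm could be taken as showing which outcomes the intervention moved.

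**Working it through.** **Inputs from the article (Participants, sample-size paragraph).** ICC 0.05-0.10; median of 18 children per preschool with 30% attrition, so m = 18 × 0.7 = 12.6 (stated as 13); coefficient of variation of cluster size 0.65; "group ratio 1:1"; about 400 children and 30 preschools per arm; "correlation of repeated measurements = 0.6-0.7"; stated design effect 1.85-2.69. The Physical activity section gives a set of 33 intensity variables.

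**Step 1: reproduce the design effect.** DE = 1 + ((1 + CV²)m − 1) × ICC, with (1 + 0.65²) × 12.6 − 1 = 16.92.
- ICC 0.05: 1 + 16.92 × 0.05 = 1.85
- ICC 0.10: 1 + 16.92 × 0.10 = 2.69

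This matches the stated range. The detectable effect, (1.96 + 0.84) × √(2 × DE × 2(1 − r)/400), is 0.21-0.24 at ICC 0.05 and 0.25-0.29 at ICC 0.10. That fits the stated effect size "of 0.25-0.30 at the 18-month follow-up".

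**Step 2: per-variable type I error if preschools are ignored.** Error = 2(1 − Φ(1.96/√DE)).
- DE 1.85: 1.96/1.36 = 1.44, error 14.9%
- DE 2.69: 1.96/1.64 = 1.19, error 23.2%

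For the 7-month sample, assuming 1,200/60 = 20 children per preschool and no attrition, DE is 2.37-3.75 and the error 20.3-31.1%.

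**Step 3: allow for the ICC of change.** The analysis uses changes, and the article gives no ICC for changes. If preschool effects correlate r_c over time and children's measurements correlate r, then ICC of change = ICC × (1 − r_c)/(1 − r).
- r_c = 0.65: about 0.04-0.12, close to the stated ICC range.
- r_c = 0.9: from 0.05 × 0.1/0.4 = 0.0125 to 0.10 × 0.1/0.3 = 0.033. DE is then 1.21-1.56 and the per-variable error 7.5-11.7%. At the middle value r = 0.65 the ICC of change is 0.014-0.029 and the error 8-11%.

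**Step 4: whole-pattern false positives under no effect.** Simulated trials had 60 preschools, mean size 12.6, CV 0.65 and a one-component partial least squares discriminant model of change on group, tested at 5% by permuting group labels across children. Model form, test, inter-variable correlation and every number of variables except 33 are assumptions.

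| Variables | Correlation between variables | ICC of change 0.05 | ICC of change 0.10 |
|---|---|---|---|
| 6 | 0.3 | 32% | 55% |
| 15 | 0.3 | 28% | 63% |
| 33 | 0.3 | 23% | 40% |
| 33 | 0.7 | 7% | 15% |
| 33 | 0 (separate run) | 76% | 99% |

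In the separate run, with 33 variables and an ICC of change of only 0.013-0.033, the rates were 23-62% at correlation 0, 10-22% at 0.3 and 6-7% at 0.7. Permuting whole preschools gave 2-8% across all settings, mostly within simulation error of 5%. Each setting used 200 or 300 trials, so a standard error is at most √(0.25/200) = 3.5 percentage points.

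**The case against.** This is a condensed article. It promises to account for clustering in all analyses, and naming separate software for one method does not withdraw that promise. Validation and resampling details of an exploratory method are usually left to a fuller plan. The simulated procedure is not in the text. The ICC values are not given as ICCs of change, and for physical activity 0.10 is an upper bound. The 33 variables are adjacent intensity bands, so substantial correlation between them is plausible, and the article does not say that they are the set related to group. The analysis only supports interpretation; effects are tested by time-by-group interactions in models that handle clustering.

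All of this limits the size and the wording of the point, and three stronger readings fail because of it.
- A reader might infer that the protocol has decided to treat children as independent. It leaves the matter open and does not say so.
- A reader might infer that a false intervention pattern is to be expected often. That needs child-level resampling, an appreciable ICC of change and variables that are not highly correlated, and none of these is stated.
- A reader might link the preference for patterns of effects over p-values to this method, and conclude that a false pattern would feed straight into the trial's conclusions. That preference stands in the paragraph on the main analyses and does not mention multivariate pattern analysis.

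The conflict itself remains. The only named means of handling clustering are the models from which this analysis is excluded. The rule on preschool averages under The Preschool Level concerns associations between individual and preschool data, and does not clearly cover children's changes related to group.

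**Conclusion.** The point holds as a conflict between two sections that leaves the handling of preschools unspecified for an analysis of a preschool-assigned factor. If children are treated as independent, per-variable type I error is about 15-23% when the ICC of change lies in the stated 0.05-0.10, and about 8-12% when preschool effects correlate 0.9 over time. For the whole pattern no single figure can be defended. At an ICC of change of 0.05-0.10 and correlations of 0.3-0.7 between variables, the simulated range is roughly 7-63%. It is higher with uncorrelated variables, and close to 5% when variables are highly correlated and the ICC of change is low. The direction is the same throughout, and resampling by preschool removes the excess. The main LMM effect tests are not biased by this; only the supportive interpretation is exposed.

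**What to change.** Reconcile the two sections by stating that, for every multivariate pattern analysis with group as the outcome:
- cross-validation leaves out whole preschools;
- significance comes from permuting group by preschool within wave, since the waves are randomized separately;
- intervals for variable importance come from resampling preschools;
- the analysis is labelled exploratory.

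If the named software cannot do this, run these models in software that can. The change needs no new data and no change of design. It costs a short addition to the plan and some extra analysis work, and fewer pattern variables are likely to be declared significant.
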